# Brief Summary/Abstract

Obesity is a major health concern that has been associated with an estimated 2.8 million deaths worldwide each year. The number of individuals considered obese with a Body Mass Index (BMI) above 30 kg/m^2^ has grown to more than 500 million. The increased morbidity and mortality associated with obesity stems from a long list of comorbidities, including hypertension, coronary artery disease, stroke, cancer, and type 2 diabetes (T2D). Bariatric surgery is an emerging intervention that has been used frequently to induce weight loss for obese individuals and it has been shown to improve glycemic control and insulin resistance in people at risk for type 2 diabetes. Beyond weight loss and improved glycemic control, surgery may lead to healthy improvements in inflammation, immune cells and vascular health. It is already known that exercise and weight loss from lifestyle modification can improve glycemic control, insulin resistance, levels of inflammatory cytokines, gut bacteria and arterial stiffness. However, no work has been done to examine a combination of bariatric surgery and pre-surgery lifestyle modification with diet and exercise. Recent work by our team has evidence demonstrating that health status pre-surgery has an impact on post-surgery outcomes. Such findings suggest that improvements in health status from exercise and/or caloric restriction before surgery may improve surgery outcomes as well as surgery-induced health outcomes. To date, no study has systematically examined the role of diet and/or exercise on the prevalence of surgery complications or on post-surgery weight loss, glycemic control, and insulin resistance. Moreover, no work currently exists with lifestyle modification, with or without bariatric surgery on adipose tissue derived inflammation related to immune cells or gut bacteria. Therefore, the purpose of this study is to investigate the effect of pre-surgery lifestyle intervention with diet and/or exercise on bariatric surgery outcomes. To test this objective, subjects will participate in a match paired study, based on BMI. Subjects will undergo testing of blood chemistry and related measures of health before and after lifestyle intervention, as well as 4 weeks post-bariatric surgery. The subjects will be match paired to standard care or exercise until these interventions are filled. Once standard care and exercise interventions are full subjects will then be match paired to exercise plus diet and then diet last. After the intervention all subjects will receive surgery. Post surgery outcomes will be assessed by examining surgery operating time, changes in blood chemistry, adipose tissue biopsies and other measures indicative of glucose and vascular health.

# Background

1. **Provide the scientific background, rationale and relevance of this project.**

Obesity has reached epidemic proportions in the United States (US), as ~34% of the adult population in the US is obese, defined as having a body mass index > 30 kg/m^2^. This is problematic because excess body fat has a strong association with increased mortality and is considered a chief risk factor promoting the development of chronic diseases such as atherosclerosis and type 2 diabetes (T2D). Obesity establishes a link between chronic diseases when in part elevations in circulating free fatty acids (FFA) and adipose tissue derived cytokines induce insulin resistance via inflammatory pathways (13, 14). Insulin resistance in turn promotes the accumulation of visceral abdominal fat and exacerbates hyperglycemia, unbalanced adipokine profiles (adiponectin, MCP-1 and leptin), increased white blood cells, elevated LDL cholesterol, beta-cell dysfunction, and arterial stiffness (5-7, 13-17). Additionally, dysbiosis of the gut microbiota is linked to obesity and atherosclerosis (38-40). Thus, interventions targeting reductions in excess fat are likely to lower overall cardiovascular disease (CVD) risk.

Bariatric surgery is currently used as a metabolic tool to treat obesity in large part because the Center for Diseases and Control predicts that obesity will reach 42% by 2030 in the US, and many metabolic abnormalities are improved. Roux-en-Y gastric bypass (RYGB) surgery remains the most commonly performed bariatric procedure, although the use of sleeve gastrectomy (SG) as risen in the last few year because of its efficacy for weight loss and reduced surgical complications compared with RYGB. Subsequently, RYGB and SG make up ~85% of all bariatric surgeries. Weight loss is the primary motive for bariatric surgery in obese patients. The Swedish Obesity Study, a large prospective intervention-based trial, found that bariatric surgery interventions induced 23%, 17%, and 18% body weight reduction at 2, 10, and 20 year follow-ups respectively (18). Post-surgically, RYGB has been linked to changes in gut microbial diversity that correlate with reduced adiposity, hyperglycemia, inflammatory cytokines, and inflammatory gene expression in white adipose tissue (41, 42). Bariatric surgery is also recognized as a treatment—some call it a “cure”—for T2D. In fact, the ability of bariatric surgery to reverse T2D has been recognized for more than 20 years. That notion began with a classic trial by Pories et al. who reported that 139 of 141 patients with T2D achieve normalized glucose tolerances within 10 days following RYGB (19. Since then, a meta-analysis of RYGB research has shown a mean rate of T2D remission of 83.7% (95% CI 77.3—90.1%) (20). Despite the overall success of these procedures, the durability of long-term weight loss and CVD risk reduction is highly variable as up to 30-70% of people regain weight and metabolic health issues within 2-3 years post-surgery (7) Addressing these health in the bariatric patient requires a novel approach targeted at optimizing metabolic health.

There is a growing body of evidence suggesting that pre-surgical health status—even among obese diabetic patients—predicts the likelihood of success from surgery. Recent work on this topic has attempted to predict T2D remission or non-remission following RYGB surgery by looking at patients’ pre-surgery health status and their subsequent surgery outcomes (2, 21-23). Preoperative duration of T2D greater than 10 years and poor preoperative glycemic control with an HbA1C > 10 have been cited as strong predictors of T2D non-remission (21, 22). Preoperative waist circumference—which has a strong association with accumulation of lipotoxic visceral abdominal fat—has also been linked with T2D remission status post-RYGB (23, 24). Additionally, patients who use oral hypoglycemic medications, rather than insulin injection, are more likely to achieve T2D remission (23). Recent investigations from our team have examined the metabolic determinants of T2D non-remission status after bariatric surgery (2). The chief characteristic of T2D severity is impaired pancreatic 𝛽-cell insulin secretion for the prevailing degree of insulin resistance (25, 26). The mechanism for this impairment is not completely understood, but a contributing factor in terms of obesity is that excess body fat leads to dysregulation of adipokines (leptin, PAI-1, TNF-α, adiponectin), which impair insulin signaling and secretion pathways (14, 15, 27). As such, it follows that differences in adipokine and inflammatory marker profiles, which improve concurrently with weight loss (28), may predict T2D remission or non-remission status. [name] et al. found that greater increases in circulating adiponectin and decreases in C-reactive protein (CRP) from baseline (pre-surgery) characterize T2D remission status 2 years after surgery (RYGB or SG; 2), independent of pre-existing BMI, age, sex and hyperglycemia (4, 5, 11). **Taken together, immune related inflammation appears to be a key determinant of bariatric surgery induced CV health.**

Vascular arterial stiffness is powerful independent predictor of CVD events (29), and several lines of research support the notion that chronic hyperglycemia and/or postprandial hyperglycemia per se contributes to the pathogenesis of atherosclerosis via impairments in vascular endothelial cell function (30-31). In fact, each component of the vasculature impacts oxygen, hormones and substrate delivery to metabolically active tissues. Vascular stiffness is driven by increased content and cross-linking of collagen, loss of elastin and by increased smooth muscle tone in the conduit artery wall. Changes in arterial expression, architecture and bioactivity of structural proteins may play a key role if stiffening of the artery. Nitric oxide (NO) and insulin are a potent vasodilator with atheroprotective actions in conduit vessels and important effects on resistance and terminal arterioles that regulate tissue perfusion. Consistent with alterations in adipose tissue derived inflammatory markers, immune cell activity has been associated with arterial stiffness and the progression of atherosclerosis (33, 34). Weight loss leads to improvements (reduction) in the arterial augmentation index (AIx), measured by applanation tonometry at the radial artery. Furthermore, a reduction in AIx has been associated with improvements in immune cell function and adipose tissue gene expression. For example, a 24 week study from Samaras et al. (33) that included a 12 week caloric restriction diet and sleeve gastrectomy (SG) found significant correlations between a reduction in AIx and a fall in the number of T-lymphocytes and CD3 cells. Reductions in AIx were also associated with reductions in cell surface expression of monocyte adhesion molecules, granulocyte activation molecules, and T-lymphocyte IL-2 receptors. However, this existing literature is limited by a lack of control groups to differentiate the independent effects of lifestyle change from the effects of bariatric surgery. Furthermore, existing literature has not evaluated if improvements in vascular health are seen in vitro before whole body adaptations occur. Interestingly, pre-weight loss intervention health markers such as baseline insulin resistance and CD3 lymphocyte numbers may predict greater improvements in AIx

(33). Another study examining cardiac and vascular morphological changes following SG found that aortic elasticity and LV diastolic function were improved compared to baseline at 6 and 12 month follow ups (35).

While bariatric surgery is an effective therapeutic option for inducing marked weight loss and remission of obesity-related diseases (e.g. cardiovascular disease (CVD)) (7), ~30-50% of patients who undergo this very invasive procedure redevelop many of their CVD complications (i.e. insulin resistance, dyslipidemia, hypertension, etc.) (5). Obviously, identifying pre-operative biomarkers associated with recurrence of cardio-metabolic abnormalities that could be used to counsel patients and develop approaches aimed at further enhancing successful weight loss for those undergoing bariatric surgery has tremendous clinical value. To date, nearly all clinical interventions aimed at sustained weight-loss and lower disease risk in response to bariatric surgery are applied AFTER surgery (3, 12) *In contrast,* there is no standardized medical therapy BEFORE bariatric surgery that is designed to minimize surgical-induced complications and/or enhance CVD risk reduction. Patients are typically recommended to lose 5-10% of their initial presenting weight prior to bariatric surgery based on the hypothesis that patients would have less surgical complications. Indeed, patients who are instructed to lose ~5-10% of their initial weight prior to surgery by CR had shorter operating room time, less intraoperative blood loss, less postoperative pain, and improved short-term postoperative weight loss (10). While CR (~800-12000 kcal/d) for ~4 weeks accomplished this goal in obese patients, the mechanism explaining reduced metabolic risk of surgery is unknown. In addition, no work has studied pre-operative Ex on reducing CVD risk. This is clinically important since CV mortality is significantly lowered by Ex through gains in aerobic fitness (i.e. VO2max) (2) and exercise improves quality of life (1) In fact, several studies by [name] et al. show that Ex drives reductions in insulin resistance and CVD risk through in part lowering adipose-derived inflammation (6, 8, 9). As a result, lifestyle intervention is a reasonable strategy to target cardiometabolic risk in obese patients who may undergo bariatric surgery (36, 37). **To date, however, no study has determined the role of immunometabolism before or after exercise (Ex) and/or caloric restriction (CR), with and without bariatric surgery. Secondarily, no work has investigated if exercise-induced health change before surgery can 1) reduce disease risk pre-operatively and 2) improve responsiveness to bariatric surgery. Together, investigation on how exercise and/or diet impacts immunometabolism and cardiometabolic risk in obese patients will lead to a better understanding of how to develop metabolic fitness programs for people undergoing bariatric surgery.**

# Hypothesis to be Tested

The central hypothesis is that pre-operative metabolic health is an important predictor of bariatric surgery effectiveness. We hypothesize that there is an adipose-derived immunosignature that predicts post-operative recurrence of obesity related CVD abnormalities and that targeting reductions in obesity BEFORE surgery will enhance the success of bariatric surgery on this disease risk. We expect that the combination of exercise and diet will be more successful at improving insulin sensitivity and reducing immune cell dysfunction compared to diet alone as well as expect that exercise will be superior to standard of care alone. These separate studies are expected to provide unique insight to the mechanism by which diet and/or exercise impact immune metabolism in obese patients, and this will shape the development of future studies in bariatric patients per se.

Primary Objectives:

1. **Ascertain the effects of Ex+CR vs. CR in obese subjects and Ex vs. standard of care (SC, i.e. control) BEFORE surgery on cardiometabolic risk.**
2. **Examine the effects of Ex+CR vs. CR in obese subjects and Ex vs. standard of care (SC, i.e. control) BEFORE surgery on surgical complications and quality of life.**
3. **Determine if circulating immunophenotyping after Ex+CR vs. Ex vs. CR vs. SC correlate with immune composition of adipose cell depots (omental and subcutaneous) at the time of surgery or post-intervention testing**.

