**Outcome assessments pertaining to the secondary objectives:**

1. Compare differences in omental and subcutaneous immune cell composition levels before and after surgical lifestyle interventions.
2. Compare omental and subcutaneous immune cell composition levels to circulating levels after the intervention at the time of bariatric surgery.
3. Compare differences in mean plasma adiponectin, MCP-1, leptin and C-RP levels before and after the interventions with insulin sensitivity, and immune cells.
4. Compare differences in gut bacteria before and after the interventions and associate with changes in insulin sensitivity and immune cells.
5. Identify if changes in pre-operative insulin sensitivity, weight loss, inflammation (e.g. adiponectin, etc.) and immune cells predict changes in bariatric responses 1 month post-op.
6. Correlate at the time of bariatric surgery insulin sensitivity, immune cells, and weight loss with operating time.

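### The central hypothesis makes pre-operative health the predictor of surgical response, but no listed analysis relates the pre-operative level to the 1-month result, and the one prediction analysis relates change to change

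*Protocol*

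**What the plan says.** Under Hypothesis to be Tested, the protocol gives three linked statements. The one it calls central is "The central hypothesis is that pre-operative metabolic health is an important predictor of bariatric surgery effectiveness". The second is that "there is an adipose-derived immunosignature that predicts post-operative recurrence of obesity related CVD abnormalities". The third is that "targeting reductions in obesity BEFORE surgery will enhance the success of bariatric surgery on this disease risk". The first two concern the state in which a patient comes to surgery. The third concerns improvement achieved beforehand.

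The Background carries both ideas. It says that pre-surgical health status "predicts the likelihood of success from surgery", and its examples are levels or history: HbA1c, diabetes duration and waist circumference. It also says that "no work has investigated if exercise-induced health change before surgery can" reduce risk and improve responsiveness to surgery.

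The three primary objectives contain no analysis of a pre-operative measure against a post-operative response. Two secondary outcomes come close. Outcome 5 reads "Identify if changes in pre-operative insulin sensitivity, weight loss, inflammation (e.g. adiponectin, etc.) and immune cells predict changes in bariatric responses 1 month post-op". Outcome 6 reads "Correlate at the time of bariatric surgery insulin sensitivity, immune cells, and weight loss with operating time". The plan for primary variable analysis names linear regression without naming the variables, and the same approach is carried over to secondary variables.

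**The concern.** The outcome list fixes the predictor of the 1-month response as a change, whereas the hypothesis called central concerns pre-operative health. As listed, the trial could finish with no estimate of the association it was built around, although it will hold every measurement needed.

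Outcome 5 has a second fault. Both its predictor and its response are changes. For a marker measured before the intervention, before surgery and one month after surgery, both differences contain a common reading. Random variation in that reading alone makes them correlate, and the result could be taken for prediction.

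**Working it through.** **1. Hypotheses against listed analyses**

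| Statement | Predictor implied | Listed analysis against the 1-month response |
|---|---|---|
| Central hypothesis | pre-operative level | none |
| Immunosignature clause | pre-operative profile | none using the level |
| Pre-operative reduction clause | pre-operative change | secondary outcome 5 |
| (Secondary outcome 6) | insulin sensitivity and immune cells at surgery | none; the outcome is operating time |

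**2. Data available.** The visit overview for bariatric patients schedules blood draw and MMTT at Visit 3, Visit 4 (or 12) and Visit 6 (or 14). The pre-operative level is therefore collected.

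**3. The shared reading.** Let B, P and M be one marker at baseline, before surgery and at 1 month. The protocol gives no within-person correlations, so assume equal variances (set to 1) and one pairwise correlation ρ. Nothing then links change to response.

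- Response counted from the pre-operative visit: cov(P − B, M − P) = ρ − 1 − ρ + ρ = −(1 − ρ). Each difference has variance 2(1 − ρ). The correlation is −(1 − ρ) / [2(1 − ρ)] = −0.5.
- Response counted from baseline: cov(P − B, M − B) = ρ − ρ − ρ + 1 = 1 − ρ. The correlation is +0.5.

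Both results hold for any ρ below 1. In 200,000 simulated samples of 12, with ρ of 0.5 or 0.8, the mean sample correlation was about −0.48 or +0.48. It was significant at 0.05 in about 40% of samples. Outcome 5 does not say from which visit the response is counted, so even the sign of the artefact is open.

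**4. What adjustment does for the same marker.** Replace the response by M adjusted for P. Given P, the change P − B varies only through B, so the partial correlation with M is −(ρ − ρ²)/(1 − ρ²) = −ρ/(1 + ρ). This is −0.33 at ρ = 0.5 and −0.44 at ρ = 0.8. In simulated samples of 12 it was significant in about 17% and 28%. Adjustment reduces the artefact but does not remove it under these assumptions, so same-marker pairs need cautious reading even after the fix.

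**5. What 12 completers can detect**

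- The protocol's own figures come first. A paired t-test, two-sided 0.05, 80% power, with delta 2 and SD 1.2 gives n = 5.05 (stated 5). Delta 2.4 (2.5 to 4.9) and SD 1.5 gives 5.28, so 6 (stated 6). Then 6/0.8 = 7.5, so 8 per group (stated 8). Two groups make 16 treated, and the protocol expects 12 to complete. These numbers size a mean pre/post change, not a prediction.
- For a correlation, Fisher's z gives the detectable r = tanh[(1.960 + 0.842)/√(n − 3)]. At n = 12 this is tanh(2.802/3) = 0.73. If all 16 were analysed it would be tanh(2.802/√13) = 0.65.
- At n = 12 a sample correlation must exceed 0.58 to reach significance. Power is 15% at r = 0.3, 38% at r = 0.5 and 74% at r = 0.7 (16%, 40% and 78% by simulation). These r values are assumptions, because the protocol states none.
- With k adjustment terms the divisor becomes √(n − 3 − k). With two (the outcome's pre-operative value and arm), the detectable partial correlation is tanh(2.802/√7) = 0.79. If level and change enter together, k = 3 and it is tanh(2.802/√6) = 0.82.

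**The case against.** The strongest objection is that change is a legitimate predictor. A reader might infer that the trial tests its hypothesis with the wrong variable. The protocol does not support that. The reduction clause and the Background both ask whether improvement before surgery enhances the response, and outcome 5 fits that question. Only the level part lacks an analysis.

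A reader might also infer that using change is what costs the power. That does not follow. A calculation that makes level the sole driver shows change doing worse, and the same calculation reverses if change is the driver. Low power comes from 12 completers and, at equal r, affects both predictors alike.

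Three further points carry some weight:

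- Outcome 6 does use status at surgery, and the Brief Summary counts operating time among post-surgery outcomes. It would therefore be too strong to say that status is related to no surgical outcome. Operating time is, however, not a metabolic, weight or cardiovascular response.
- The wording of outcome 5 is loose. Weight loss is already a change, so the word for change may not govern the whole list, and inflammation and immune cells could be read as levels. Exact coding may sit in an analysis plan not shown here. For insulin sensitivity, though, the protocol itself fixes the predictor as a change.
- The sample-size section calls the data preliminary work for future power analyses. This softens the power criticism but not the mismatch. Preliminary data should at least estimate the association that later studies would be sized on.

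Finally, regressing a marker's 1-month value on its own pre-operative level would mostly show that people keep their rank: heavier patients tend to stay heavier whether or not surgery worked. The remedy has to guard against this.

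**Conclusion.** The point holds in a limited form. The central hypothesis and the immunosignature clause have no listed analysis of the pre-operative level against the 1-month response. This rests on the text alone. Outcome 5 serves the reduction clause, but as a change-on-change analysis it carries an artefactual correlation of about −0.5 or +0.5 whenever the same marker is on both sides. That size assumes equal variances and equal correlations across the three visits and would differ under other structures.

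With about 12 bariatric completers, any such analysis reaches 80% power only for a simple correlation of about 0.73 or more, and for a larger one once covariates enter. A null result on either predictor would therefore say little about the hypothesis. The mismatch is worth correcting because correction is cheap, but it does not invalidate outcome 5 or the trial.

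**What to change.** Reword secondary outcome 5 as follows:

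- **Predictors.** Add the level at Visit 4 (or 12) of insulin sensitivity index, adiponectin and CRP, immune cells and weight, beside the pre-operative change in each.
- **Response.** Use the 1-month value, adjusted for the pre-operative value of that same outcome, with arm as a covariate.
- **Same-marker pairs.** Here the pre-operative level is already the adjustment term. Do not read a marker's level predicting its own unadjusted 1-month value as evidence of effectiveness. Treat a change term for the same marker with caution, and rest the interpretation mainly on pairs of different markers.
- **Status.** Label both predictors exploratory. State that about 12 completers give 80% power only for a correlation of about 0.7 or more (0.73 before covariates), and report estimates with confidence intervals.

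The cost is the rewording of one secondary outcome. The visits, assays and regression method are already planned. The drawback is one more predictor in a small regression: by the formula above, entering level and change together with the two adjustment terms raises the detectable partial correlation from 0.79 to 0.82. Fitting the two predictors in separate models limits this.
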